### **5.2.3 Sensitivity analyses**

Two sensitivity analyses will be presented: the analysis without adjustment and the analysis without imputation of missing data.

## **6 Secondary endpoint analysis**

### **6.1 Knee pain over the past 48 hours**

#### **6.1.1 Definition**

Knee pain over the past 48 hours is assessed using a numeric pain scale from 0 to 100 at the enrolment visit, preoperative visit, week 6, month 3, month 4, month 5, month 6 and month 12.

#### **6.1.2 Analysis**

The average pain assessment will be estimated in each of the groups. These averages will be compared using a longitudinal analysis. A linear mixed regression model will be used with assessment of pain at each time point (enrolment visit, preoperative visit, week 6, month 3, month 4, month 5, month 6 and month 12) as an explanatory variable with constrained longitudinal data analysis. The randomisation arm, the visit, the arm interaction per visit and the centre (adjustment variable) will be used as fixed effects and the patient (intercept + visit) and the surgeon (intercept + group) will be used as random effects. The adjusted mean differences will be derived from this model. The statistical tests will be performed at months 6 and 12.

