| Length of stay at rehabilitation care facilities   |                 |                         |                               | +                  | +                      |                    | +(a)          |                         |
| MOS SF 12                                          | +               | +                       |                               |                    | +                      |                    | +             | +                       |
| EQ-5D-3L                                           | +               |                         |                               |                    |                        |                    | +             | +                       |
| RAPT                                               | +               |                         |                               |                    |                        |                    |               |                         |
| Adaptation to environment                          |                 | +                       |                               |                    | +                      |                    |               |                         |
| Number of steps                                    | +(b)            | +(c)                    |                               |                    | +(c)                   |                    | +(c)          | +(c)                    |
| Treatment satisfaction                             |                 |                         |                               |                    |                        |                    | +             | +                       |
| Co-interventions                                   | +               | +                       |                               |                    | +                      |                    | +             | +                       |
| Adverse Events                                     |                 | +                       | +                             |                    | +                      |                    | +             | +                       |

(a) If the length of stay is longer than 6 weeks

(b) To be performed the week after the enrolment visit (7 days)

- (c) To be performed the week before the enrolment visit (7 days)

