| Number of patients        | 
300 patients will be enrolled:
150 patients in the experimental arm
150 patients in the control arm (usual information and advice given by the surgeon)
                                                                                                                                                                                                                                                                                                                                                                                                                                                                                                                                                                                                                                                                                                                                                                                                                                                                                        |
| Selection criteria        | 
Inclusion criteria:
 
 
- Men or women aged from 50 to 85 years;
 
- Patients with knee osteoarthritis according to the ACR criteria for which a total knee arthroplasty has been scheduled by the surgeon;
 
- Preliminary medical examination, the results of which will be communicated to the patient;
 
- Patients having provided their written informed consent to take part in the study;
 
- Patients affiliated with a social security scheme (beneficiary or entitled party).
 
 
Exclusion criteria:
 
 
- Institutionalised patients;
 
- Patients having already undergone ipsilateral total knee arthroplasty;
 
- Patients with chronic inflammatory arthritis;
 
- Cognitive or behavioural disorders making the assessment impossible;
 
- Difficulties in understanding and communicating in French;
 
- TKA for an indication other than knee osteoarthritis.
 
 |

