## **4 Principles of analysis**

### **4.1 General principles for the endpoint analysis**

The results will be reported in line with the CONSORT 2010 recommendations.

The endpoint analysis will be carried out in the ITT population.

The statistical analysis will be carried out with blinding in terms of the randomisation group.

No interim analysis is planned for this trial.

All the endpoints will be tested for superiority.

As the analyses are based on modelling or other numerical approaches, they require verification of the underlying hypotheses as well as convergence of their algorithms. If these conditions are not verified, an alternative method will be used.

The analyses will be carried out using R software version 3.4.4 or later (The R Foundation for Statistical Computing, Vienna, Austria).

The tests used will be bilateral with a significance threshold of 2.5% for the two primary endpoints and 5% for the secondary endpoints. The 2.5% threshold was chosen to take into account the double primary endpoint.

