## **6.3 Quality of life**

### **6.3.1 Definition**

Quality of life is assessed using the MOS SF-12 and EQ-5D scales.

For the SF-12, the physical (PCS) and mental (MCS) health scores will be calculated at the enrolment visit, preoperative visit, month 3, month 6 and month 12.

The EQ-5D is collected at the enrolment visit and at months 6 and 12; it will be used for the health economics analysis.

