### **6.5.2 Analysis**

The average treatment satisfaction scores will be estimated in each of the groups. These averages will be compared using a longitudinal analysis. A linear mixed regression model will be used with the score at each time point (month 6 and month 12) as the response variable. The randomisation arm, the visit, the arm interaction per visit and the centre (adjustment variable) will be used as fixed effects and the patient (intercept + visit) and the surgeon (intercept + group) will be used as random effects. The adjusted mean differences will be derived from this model. The statistical tests will be performed at months 6 and 12.

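### The secondary mixed models are over-parameterised when visit is categorical, and their listed arm main effect contradicts the baseline constraint

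*Supplement*

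**What the plan says.** SAP sections 6.1.2 (pain), 6.2.2 (personalised WOMAC), 6.3.2 (SF-12), 6.4.2 (steps) and 6.5.2 (satisfaction) share one model sentence. The fixed part reads "The randomisation arm, the visit, the arm interaction per visit and the centre (adjustment variable) will be used as fixed effects". The random part follows in the same sentence: "as fixed effects and the patient (intercept + visit) and the surgeon (intercept + group) will be used as random effects". Tests are at months 6 and 12. Neither the coding of visit in the random part nor any covariance structure is given.

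Sections 6.1.2 to 6.4.2 add that the analysis is a constrained longitudinal one. Section 6.5.2 does not: it takes the model "with the score at each time point (month 6 and month 12) as the response variable", and there is no baseline satisfaction score.

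SAP 4.1 asks for assumptions and convergence to be checked. It then says: "If these conditions are not verified, an alternative method will be used". The same section says that the analysis is blind to group and will be run in R.

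For steps, SAP 6.4.1 takes the enrolment value from the week after the enrolment visit, as does note (b) to the table in the protocol's general outline of the study. Protocol VII.1 places randomisation at that visit, and protocol III.3 and V.3 say that patients cannot be blinded.

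**The concern.** There are three separate problems.

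1. **Random effects.** A patient intercept plus a categorical visit effect gives each patient as many random effects as observations. A residual variance on top of that cannot be separated from them.
2. **Baseline constraint.** Constrained longitudinal analysis gives both arms one common baseline mean. An arm main effect together with a full arm-by-visit interaction estimates a separate baseline mean for each arm. The text therefore names one model and lists the terms of another.
3. **Steps.** The common baseline mean is justified when baseline precedes allocation. The step week comes after patients know their arm.

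The stake is pre-specification of the clinical secondary comparisons. Two analysts could follow this text to different models, and the plan does not say which comes next if the fit stops. Both primary endpoints have their own models (SAP 5.1.2 and 5.2.2) and are not affected.

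**Working it through.** The documents give no power or precision figure for these models, so there is none to reproduce.

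**Inputs.** "300 patients will be enrolled". Pain and personalised WOMAC have 8 visits ("enrolment visit, preoperative visit, week 6, month 3, month 4, month 5, month 6 and month 12"), SF-12 has 5 ("enrolment visit, preoperative visit, month 3, month 6 and month 12"), steps have 6 by SAP 6.4.1 (the seven daily counts are averaged to one value per visit), and satisfaction has 2.

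**1. Covariance parameters, visit categorical.** With K visits, K(K+1)/2 variances and covariances can be estimated. An intercept plus K−1 visit effects already uses K(K+1)/2, and the residual variance adds one.

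| Outcome | K | Estimable | In the model |
|---|---|---|---|
| Pain, personalised WOMAC | 8 | 8×9/2 = 36 | 37 |
| Steps | 6 | 6×7/2 = 21 | 22 |
| SF-12 | 5 | 5×6/2 = 15 | 16 |
| Satisfaction | 2 | 2×3/2 = 3 | 4 |

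On simulated data (15 surgeons assumed), R's lme4 stopped for the 8-visit model, since 300×8 = 2400 observations do not exceed 300×8 = 2400 random effects. It stopped for satisfaction at 600 against 600.

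**2. Visit numeric in the random part.** A random intercept and slope need 2 variances, 1 covariance and 1 residual, 4 in all. That is identified for 8, 6 or 5 visits. For satisfaction it is again 4 against 3, and lme4 again stopped.

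**3. Do the arm contrasts survive?** I took a simulated 8-visit trial of 300 patients (assumed SD 20, within-patient correlation 0.5, 10% missing after baseline) and varied the residual variance from 1.5 to 132.9. The log-likelihood stayed at −9201.78 and the constrained month-6 contrast at −7.73 (SE 2.11). Only the split between patient and residual variance is undetermined. The contrast is that of an unstructured-covariance model.

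**4. Baseline constraint.** Eight visits in two arms give 16 means, and a common baseline leaves 15. Arm plus full arm-by-visit frees all 16. The freed mean is the baseline arm difference. In the same simulated trial:
- constrained: month 6 −7.73 (SE 2.11), month 12 SE 2.12;
- arm effect kept: month 6 −7.32 (SE 2.32), month 12 SE 2.42;
- interaction coefficient read alone: −7.32 − 0.95 = −8.27, where 0.95 is the chance baseline difference.

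The variance ratios are (2.32/2.11)² = 1.21 and (2.42/2.12)² = 1.30. For complete data the ratio is 1/(1−r²), with r the correlation of baseline with follow-up. It is 1/(1−0.09) = 1.10 at r = 0.3 and 1/(1−0.36) = 1.56 at r = 0.6. The documents give no r.

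**5. Steps.** Let d be an arm difference in the baseline week caused by knowing the allocation. With equal SDs and complete data, the constraint shifts the later contrast by −r×d. The documents give neither r nor d. Protocol VII.1 caps the wait for the programme at one month and sets no minimum.

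**The case against.** A reader might infer that these models cannot be estimated at all, so that every clinical secondary result would rest on a substitute. The documents do not support that. The SAP does not fix the coding of visit, and a numeric random slope is identified for everything except satisfaction. Even with categorical visit, the contrasts are determined and the obvious repair leaves them unchanged. A numeric slope would also not force mean trajectories into a straight line through surgery if the fixed visit effect stays categorical. It restricts only patients' deviations from the mean.

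The inference that a model would be picked by its result is also too strong. SAP 4.1 keeps the analysis blind to group, and protocol IX.4 (secondary endpoint analysis) describes a repeated-measures model with the initial value as a fixed effect. That limits the scope for selection. It does not settle the model, because the SAP does not name the protocol's version as its fallback.

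On the constraint, naming the method can be read as dropping the arm term, with the list as a loose inventory. That reading is possible, but the list is explicit, and 6.5.2, where no constraint applies, has the same list.

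On steps, both arms wear the pedometer. The 20% target for sedentary patients comes only with the first education session, so a difference in the first week is conjecture. The lost constraint and the steps bias are also alternatives: the first arises if the constraint is dropped, the second if it is imposed.

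**Conclusion.** The specification needs correcting, but the treatment estimates are recoverable.

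- **Over-parameterisation** by one holds for every outcome if visit is categorical. That is the natural reading, since arm-by-visit is tested at named months. For satisfaction it holds under either coding.
- **The constraint conflict** holds for 6.1.2 to 6.4.2 and not for 6.5.2. Its cost, if the terms are fitted as listed, is precision: about 10% to 56% more variance for an assumed r of 0.3 to 0.6. It is not a bias.
- **For steps**, randomisation does not guarantee the equal baseline. A reader might go further and infer a known bias in the step comparison, but the documents give nothing from which to size it.
- **No fallback is named** in SAP 4.1, so the model that follows a failed fit is not pre-specified.

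The simulated figures rest on the SD, correlation, missingness and number of surgeons assumed above. The parameter counts rest only on the visit lists.

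**What to change.** Amend the SAP wording as follows.

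1. **Sections 6.1.2 to 6.3.2:** state that visit is categorical, with an unstructured within-patient covariance and no patient random effects. Keep centre and the surgeon effect. Use visit and arm-by-visit at post-baseline visits only, with no arm main effect. Call the score the response in 6.1.2 to 6.3.2, where it is now called explanatory.
2. **Section 6.4.2 (steps):** use the same covariance, but do not constrain or adjust for the week after randomisation. Fit arm, visit and arm-by-visit to the later visits.
3. **Section 6.5.2 (satisfaction):** fit arm, visit and arm-by-visit with a 2×2 unstructured covariance, keeping centre and the surgeon effect.
4. **Section 4.1:** name an ordered list of simpler covariance structures to be tried in turn if the model does not converge.

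The cost is a text change with no new data. The one statistical price is some precision for steps, because the enrolment week no longer contributes.

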### **6.2 Function**

#### **6.2.1 Definition**

Function is assessed using the personalised WOMAC scale at the enrolment visit, preoperative visit, week 6, month 3, month 4, month 5, month 6 and month 12.

### **6.2.2 Analysis**

The average personalised WOMAC score will be estimated in each of the groups. These averages will be compared using a longitudinal analysis. A linear mixed regression model will be used with the score at each time point (enrolment visit, preoperative visit, week 6, month 3, month 4, month 5, month 6 and month 12) as an explanatory variable with constrained longitudinal data analysis. The randomisation arm, the visit, the arm interaction per visit and the centre (adjustment variable) will be used as fixed effects and the patient (intercept + visit) and the surgeon (intercept + group) will be used as random effects. The adjusted mean differences will be derived from this model. The statistical tests will be performed at months 6 and 12.

## **6.3 Quality of life**

### **6.3.1 Definition**

Quality of life is assessed using the MOS SF-12 and EQ-5D scales.

For the SF-12, the physical (PCS) and mental (MCS) health scores will be calculated at the enrolment visit, preoperative visit, month 3, month 6 and month 12.

The EQ-5D is collected at the enrolment visit and at months 6 and 12; it will be used for the health economics analysis.

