## **1.2 - EXPECTED RESULTS AND PROSPECTS**

The study will be conducted in patients between the ages of 50 and 85 years with knee osteoarthritis for which total knee arthroplasty has been scheduled by the surgeon. Two patient groups will be studied: one of the two groups will undergo four group sessions including therapeutic education and physical exercises, a knee arthroplasty guide and an exercise CD at least 2 months before the intervention; the other group (control group) will receive the usual information and advice given by the surgeon and according to each centre, and a knee arthroplasty guide.

If this programme is confirmed to be effective, it should lead to a reduction in the length of hospital stay and rate of transfers to rehabilitation care facilities, achieving quicker and more complete functional recovery, improving the patient's quality of life and satisfaction, and reducing treatment costs.

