### **II.2 - SECONDARY OBJECTIVES**

The secondary objectives in these patients with knee osteoarthritis for whom a TKA is scheduled are as follows:

1) Clinical assessment at 6 months and 12 months:

- a. function (WOMAC);
- b. pain (numeric scale 0-100);
- c. quality of life (SF-12 and EQ-5D-3L);
- d. number of steps (pedometer);
- e. treatment satisfaction.

2) Health economics evaluation for the intervention. The costs of the two strategies will be compared at 6 and 12 months by taking into account the perspectives of the payer (Health Insurance) and the healthcare system. In addition, patients' quality of life will be estimated at the enrolment visit, and 6 months and 12 months after the procedure, using the EuroQoL questionnaire (EQ-5D-3L) [Brooks 1996, Fransen 1999] (Annex 5). In the event that the most expensive strategy is the one that provides the best medical outcome and the best quality of life, we will carry out a cost-effectiveness analysis.

Implementing and evaluating complex intervention strategies such as combining educational and supervised exercise programmes is complicated and raises a number of specific methodological issues. Recently published recommendations [Craig 2008] highlight the need to take into account multiple endpoints. Indeed, complex interventions have multiple objectives (improving function, patient information and changing patient behaviour in terms of physical activity and weight-loss).

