### **VII.3 - FOLLOW-UP VISITS AFTER THE INTERVENTION**

#### **VII.3.1 - PREOPERATIVE VISIT (V1)**

At the preoperative visit, which will take place one or two days before the surgery, the following information will be collected in the electronic case report form:

- Professional status;
- Number of steps measured by the patient in the week (7 days) before this visit;
- Co-interventions since the enrolment visit;
- Adverse events.

Patients will fill in a self-assessment card including assessment of the following:

- knee pain over the past 48 hours (numeric scale);
- function according to the WOMAC scale and the personalised section;
- quality of life (MOS SF-12);
- adaptation of environment.

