### **VII.3.3 - CONTACT BY POST OR EMAIL 6 WEEKS AFTER SURGERY**

Patients will fill in a self-assessment card including assessment of the following:

- knee pain over the past 48 hours (numeric scale);
- function according to the WOMAC scale and the personalised section;
- a question on the length of stay at rehabilitation care facilities.

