#### **VII.3.6 - CONTACT BY POST OR EMAIL 6 MONTHS AFTER SURGERY**

Patients will fill in a self-assessment card including assessment of the following:

- knee pain over the past 48 hours (numeric scale);
- function according to the WOMAC scale and the personalised section;
- number of steps measured by the patient in the week before this contact;
- quality of life (MOS SF-12 and EQ-5D-3L);
- length of stay at rehabilitation care facilities;
- treatment satisfaction;
- co-interventions since the previous visit;
- adverse events.

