## **8 Health economics analysis**

The EQ-5D scores will be converted into utilities based on French value tables. The utilities imputed for the periods corresponding to the interval between 2 collections will be multiplied by the corresponding durations to obtain QALYs. The differences in QALYs will be compared between the two groups.

The intervention will be valued on a flat-rate basis based on the time spent by the professionals as described in the protocol and by multiplying the estimated cost of each session by the proportion of patients having undergone the sessions.

Hospital admissions related to the pathology (imputed during the end-of-study meeting) will be valued based on 1) ENCC (French national hospital costs study database) costs and 2) rates. The costs will be estimated for each patient and the average costs in each arm will be compared using non-parametric tests.

The incremental cost-utility ratio will be calculated by comparing the difference in average costs with the difference in average QALYs, with a bootstrap sensitivity analysis.

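### No EQ-5D is collected between enrolment and month 6 after surgery, so a utility difference confined to the wait and early recovery cannot enter the QALY, and a later one is captured inaccurately

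*Supplement*

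**What the plan says.** The latest protocol and the latest SAP (version 2.0) agree on the schedule. Protocol II.2 says that "quality of life will be estimated at the enrolment visit, and 6 months and 12 months after the procedure, using the EuroQoL questionnaire", and the schedule table in section VII marks the same three columns. SAP 6.3.1 repeats it: "The EQ-5D is collected at the enrolment visit and at months 6 and 12; it will be used for the health economics analysis".

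The contacts in between carry other instruments:

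- Preoperative visit (Protocol VII.3.1): "quality of life (MOS SF-12" only, with pain and WOMAC.
- Week 6 (VII.3.3): pain, WOMAC and "a question on the length of stay at rehabilitation care facilities". There is no quality-of-life scale.
- Month 3 (VII.3.4): SF-12, pain and WOMAC, but no EQ-5D.
- Months 4 and 5 (VII.3.5): WOMAC and pain.
- Month 6 (VII.3.6): "quality of life (MOS SF-12 and EQ-5D-3L"), the first utility measurement after surgery.

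For the SF-12, SAP 6.3.1 says the two component scores "will be calculated at the enrolment visit, preoperative visit, month 3, month 6 and month 12".

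SAP 8 then builds the QALY: "The utilities imputed for the periods corresponding to the interval between 2 collections will be multiplied by the corresponding durations to obtain QALYs". It does not say how the utility for an interval is imputed, and it plans no use of the SF-12 for this purpose.

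**The concern.** Protocol II.1 makes the speed of recovery in the first six months after surgery a co-primary objective, and WOMAC is measured densely to capture it: enrolment, preoperatively, week 6, and months 3, 4, 5 and 6. Utility is not measured at all inside that window. The programme also acts before the operation. One session deals with preoperative anxiety, and anxiety/depression is one of the five EQ-5D dimensions, yet no EQ-5D is taken between the sessions and month 6 after surgery.

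At stake is the secondary cost-utility objective. The trial could show faster recovery on the WOMAC area under the curve and no QALY difference, purely because of when utility was measured. The gap is neutral as to benefit or harm: a passing loss of utility, for example from the exercise-related pain listed in Protocol X.2, would be missed in the same way. Protocol II.2 also calls for a cost comparison at 6 months, and at that point only two utility values per patient exist.

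**Working it through.** **Length of the gap.** Protocol VII.1 allows up to 1 month from enrolment to the start of the programme. V.1 puts that start at least 2 months before surgery. Follow-up runs to 12 months after surgery.

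- Total: (0 to 1) + 2 + 12 = 14 to 15 months, which reproduces Protocol III.2.
- Enrolment to month 6: (0 to 1) + 2 + 6 = 8 to 9 months.
- Share: 8/14 = 57%; 9/15 = 60%.

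The 2 months is a minimum, so the gap may be longer in practice.

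**A difference that closes by month 6.** Randomisation makes the arms equal in expectation at enrolment. If they are equal again at month 6, any common rule that uses only these two values gives both arms the same expected utility over the interval. The expected QALY difference is 0, whatever happened in between.

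**Other trajectories.** The documents give no utilities, so the differences between arms below are assumed. Surgery is placed 3 months after enrolment. QALY difference = trapezoidal area of the utility difference ÷ 12, with linear interpolation (also an assumption). The differences stand at months −3, 0, 1.5, 3, 6 and 12 from surgery. The planned schedule uses −3, 6 and 12; the amended one uses −3, 0, 3, 6 and 12.

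| Assumed differences | All six points | Planned | Amended |
|---|---|---|---|
| A. Early, fades: 0, 0.05, 0.10, 0.05, 0, 0 | 0.031 | 0 | 0.025 (80%) |
| B. As A, 0.02 left at month 6 | 0.039 | 0.0125 (32%) | 0.0325 (84%) |
| C. Early, none before surgery: 0, 0, 0.10, 0.05, 0, 0 | 0.022 | 0 | 0.0125 (57%) |
| D. Sustained: 0, then 0.05 throughout | 0.056 | 0.044 (78%) | 0.056 (100%) |
| E. Late: 0 up to month 3, then 0.05, 0.05 | 0.031 | 0.044 (140%) | 0.031 (100%) |

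For A in full: (3×0.025 + 1.5×0.075 + 1.5×0.075 + 3×0.025)/12 = 0.375/12 = 0.031. Amended: (0.075 + 3×0.05 + 0.075)/12 = 0.30/12 = 0.025.

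For E in full: (3×0.025 + 6×0.05)/12 = 0.375/12 = 0.031. Planned: (9×0.025 + 6×0.05)/12 = 0.525/12 = 0.044.

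D and E give the planned schedule the same data and so the same 0.044, although one is worth 0.056 and the other 0.031. If surgery is 2 months after enrolment, D is captured at 0.0417/0.0542 = 77%.

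C shows what week 6 adds. Its peak falls there, so the preoperative and month 3 values alone recover only 57%.

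**The unstated rule.** Take differences of 0, 0.05 and 0.05 at enrolment, month 6 and month 12. Linear interpolation gives 0.044. Carrying each value forward gives 0.05×6/12 = 0.025. Carrying each value back gives 0.05×15/12 = 0.0625. All three are compatible with the wording of SAP 8.

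**The case against.** A reader might infer that the QALY skips the early period, that this is the only period in which the programme could gain utility, or that the cost-utility ratio is biased against the programme. The documents support none of these.

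- The period is counted, with imputed utility. What is missing is a measurement inside it.
- Protocol I.2 expects the programme to work by "achieving quicker and more complete functional recovery, improving the patient's quality of life and satisfaction, and reducing treatment costs". A more complete recovery would leave a difference at months 6 and 12, where quality of life is a stated target (II.2), and that difference would enter the QALY.
- The direction of error is not fixed. In scenario E the planned schedule overstates the gain, because interpolation credits it back over the wait and the operation.
- The cost side is not blind to early benefit. Protocol IX.4 lists length of stay in hospital and in rehabilitation among the resources, and SAP 8 values admissions. SAP 8 also weights programme cost by the proportion of patients who underwent the sessions.

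There are practical objections too. The SAP was validated on 29/03/2018 and the documents do not give recruitment status. Added collections may come too late for some or all patients, and a change midway would leave patients on different EQ-5D grids. Predicting utility from the SF-12 is no full substitute: most SF-12 items recall the past 4 weeks while the EQ-5D asks about today, and the relation could not be checked at the preoperative visit or month 3. This stands, and it is why a predicted curve belongs in a sensitivity analysis.

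Finally, the schedule is internally consistent and concerns a secondary economic objective. Under Protocol II.2 the cost-effectiveness analysis is undertaken only if the costlier strategy also has the better outcome.

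**Conclusion.** The point holds in this form. EQ-5D has no collection for 8 to 9 of the 14 to 15 months of follow-up, an interval that includes the whole co-primary recovery window. A utility difference confined to it contributes zero to the expected QALY difference. This needs only that the imputation uses the two end values, and it does not depend on the utilities assumed. A difference persisting at month 6 or 12 is recorded, but with an error whose sign depends on the trajectory: 32% to 140% of the full value in scenarios B, D and E. Those percentages rest on assumed utilities and linear interpolation and are illustrations only.

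The schedule itself is certain; the size and direction of the error are not. Neither primary endpoint is affected, nor is the safety analysis. The change is worth making because it costs little and lets the QALY reflect the period in which faster recovery is expected.

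**What to change.** 1. Add the EQ-5D-3L to the preoperative self-assessment card (Protocol VII.3.1) and the month 3 self-questionnaire (VII.3.4), ideally also to the week 6 questionnaire (VII.3.3). Amend the schedule table and SAP 6.3.1 to match.
2. In SAP 8, compute QALYs over all collected points and state the interpolation rule. If the change is made midway, say how patients enrolled before and after it are combined.
3. Where those contacts are already past, keep the measured EQ-5D at enrolment, month 6 and month 12 as the base case, still with a stated rule. Pre-specify a sensitivity analysis in which utility at the preoperative visit and month 3 is predicted from the SF-12 collected there, using the relation between SF-12 and EQ-5D utility estimated in this trial at enrolment, month 6 and month 12. Report that no utility was measured in between.

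Cost: five more questions at two or three contacts where patients already complete questionnaires, plus the amendment. If collection is closed, the cost is SAP wording and a modelled relation used only as sensitivity.
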